## Abstract

**Background:**

Depression is a common antenatal mental disorder and is associated with an increased risk of adverse effects on the fetus and significant morbidity for the mother; if untreated it can also continue into the post-natal period and affect mother-infant interactions. There has been little research evaluating the effectiveness or cost-effectiveness of antenatal psychological interventions for antenatal depression, particularly for mild to moderate disorders. International guidelines recommend a stepped care approach starting with Guided Self Help, and the aim of this exploratory trial is to investigate Guided Self Help modified for pregnancy.

**Methods:**

The DAWN trial is an exploratory randomised controlled trial of the effectiveness and cost-effectiveness of antenatal Guided Self Help, modified for pregnancy and delivered by National Health Service Psychological Wellbeing Practitioners. Antenatal Guided Self Help, in addition to usual care, is compared with usual care for pregnant women diagnosed with mild to moderate depression and mixed anxiety and depression, using the Structured Clinical Interview for DSM-IV Disorders. Modifications for pregnancy include perinatal mental health training, addressing pregnancy-specific worries and including sections on health issues in pregnancy and planning for parenthood. Women allocated to Guided Self Help will be seen for up to eight sessions by a Psychological Wellbeing Practitioner (including an initial assessment session); there will also be an appointment at 12 weeks after delivery. Research measures including the Edinburgh Postnatal Depression Scale (primary outcome) and other measures of depression, anxiety, quality of life and service use will be collected from women before random allocation, 14 weeks after random allocation and at 12 weeks after delivery. Potential psychological mechanisms of the intervention will be explored using the Pregnancy-Related Thoughts Questionnaire and the Metacognitive Awareness Questionnaire.

**Discussion:**

The DAWN trial is the first exploratory trial to investigate the efficacy of antenatal Guided Self Help for pregnant women with mild to moderate depression meeting DSM-IV diagnostic criteria. Recruitment started January 2015 and is expected to be completed by July 2016.

**Trial registration:**

ISRCTN registry: ISRCTN83768230. Registered on 8 August 2014.

**Electronic supplementary material:**

The online version of this article (doi:10.1186/s13063-016-1632-6) contains supplementary material, which is available to authorized users.

## Background

Pregnancy does not appear to be protective against the persistence or development of psychiatric disorders [1]. Depression is the most common antenatal mental disorder with a 9 % period prevalence [1], which is similar to that for non-pregnant childbearing-aged women. Depression in pregnancy can have a considerable impact upon the woman and her family, and is associated with an increased risk of (1) adverse effects on the fetus, including low birth weight and preterm delivery [2]; (2) infant deaths [3]; (3) post-natal maternal psychopathology [4–6]; (4) subsequent behavioural/emotional problems in the child and adolescent [7]; and (5) negative impacts on other family members [8]. Such adverse outcomes are not inevitable, and early effective interventions could mitigate these effects. Since mental disorders in pregnancy are also associated with other risk factors that may lead to adverse outcomes, particularly smoking [9, 10], socio-economic deprivation [11], obesity [12] and domestic violence [13, 14], consideration of associated risk factors should also be included in the development of interventions. International guidelines recommend that there should be a higher threshold for medication than at other times in a woman’s life due to the potential risk to the fetus, as well as a lower threshold for offering psychological therapies [15]. To date there has been little research evaluating the effectiveness of antenatal psychological interventions for the most common disorder: mild and moderate antenatal depression.

Cochrane reviews have reported limited evidence on the effectiveness of small trials of interpersonal therapy, massage and acupuncture [16, 17], and there have only been three recently completed pilot randomised controlled trials of cognitive behavioural therapy (CBT) [18–20]. To our knowledge, there has been no evaluation of less intensive psychological interventions for women diagnosed with mild and moderate depression in the antenatal setting — interventions which may be more cost-effective.

The National Institute for Health and Care Excellence (NICE) [15] recommends a stepped care approach for depression, starting with Guided Self Help, a low-cost intervention for mild and moderate depression which is delivered by Psychological Wellbeing Practitioners. Recent UK national policy highlights the importance of improving access to psychological therapies for women in the perinatal period [21]. A recent systematic review and meta-analysis of Guided Self Help for mild and moderate depression found evidence of effectiveness post-treatment but limited effectiveness at long-term follow-up, with variability across different settings [22]; no trials in perinatal settings were included. However, an Australian study of an antenatal supported self help intervention for the prevention of perinatal common mental symptoms reported reduced depressive symptoms at 12 weeks post-delivery [23]. Moreover, in the antenatal period even short-term improvement in mild disorders is important, as there is evidence that mild disorders can adversely affect fetal outcomes [2]. Although psychological interventions in the antenatal setting which are less intensive may be more cost-effective for mild and moderate antenatal depression, there has been no evaluation of this approach. We therefore propose to evaluate a new form of Guided Self Help for antenatal depression in women using UK National Health Service (NHS) maternity services in an exploratory randomised controlled trial (RCT).

The objectives of this exploratory trial are to:Establish recruitment and follow-up ratesIndicate levels of compliance with the interventionIndicate for whom the intervention is most suitableProvide preliminary evidence for the efficacy of the intervention (estimating treatment effect sizes)Provide preliminary evidence for the cost-effectiveness of the intervention compared to usual careExplore the psychological mechanisms of the intervention.

We will test our procedures within large maternity services in English NHS settings [24]. The NHS is the publicly funded healthcare system for England. It provides healthcare to every legal resident in the United Kingdom, with mental health and primary care among the services free at the point of use.

There are four specific main aims of this trial: (1) to establish that the trial procedures work (and fine-tune where necessary) so that a Phase III trial can follow; (2) to evaluate whether antenatal Guided Self Help is beneficial in improving depressive symptoms for women with antenatal depression; (3) to evaluate whether antenatal Guided Self Help has the added benefit of improving other outcomes, including post-treatment and post-delivery psychological symptoms, post-delivery bonding and quality of life; and (4) to explore whether antenatal Guided Self Help is likely to be cost-effective compared to usual care. The latter two aims will also estimate treatment effect sizes.

The following hypothesis will be tested:

Women with mild or moderate antenatal depression treated with Guided Self Help will have significantly lower Edinburgh Postnatal Depression Scale (EPDS) depressive symptoms at 14 weeks post-randomisation compared to women with mild or moderate antenatal depression receiving usual care.

## Methods/design

This study has been designed according to the Standard Protocol Items: Recommendations for Interventional Trials (SPIRIT) statement. Additional file 1: Table S1 presents the SPIRIT checklist, and Additional file 2: Figure S1 presents the SPIRIT figure for the schedule of enrolment, intervention and assessments.

The trial is a multi-centre Phase II exploratory randomised controlled trial with two parallel groups and a primary endpoint of EPDS depressive symptoms at 14 weeks post-randomisation.

Pregnant women with depression will be randomly allocated to either Guided Self Help plus usual care or to usual care alone (i.e. treatment as usual). Randomisation, stratified by type of depression (i.e. mild or moderate depression, or mixed anxiety and depression), will be performed using block randomisation of varying sizes with a 1:1 allocation.

### Study setting

The study setting is inner city English NHS maternity services in South East London serving an ethnically and socially diverse population.

### Eligibility criteria

#### Inclusion criteria

Women must have the following characteristics prior to randomisation:Aged ≥16 yearsPregnant, not exceeding 26 weeks gestationMeet criteria for Diagnostic and Statistical Manual of Mental Disorders (DSM)-IV depression (mild or moderate major depressive disorder, or mixed anxiety and depressive disorder) on the Structured Clinical Interview DSM-IV (SCID)Able to provide informed consent.

#### Exclusion criteria

The exclusion criteria are as follows:Pregnant women receiving cognitive behavioural therapy or another individual or group psychological therapyPregnant women taking antidepressantsPregnant women suffering from psychosis, current eating disorder, borderline personality disorder or current post-traumatic stress disorder, or receiving care from secondary mental health servicesPregnant women who are unable to complete questionnaires or follow the trial workbook in EnglishPregnant women who endorse ‘yes, quite often’ on question ten of the Edinburgh Postnatal Depression Scale (EPDS) or other measures of suicidality (e.g. at least two items of the SCID on suicidality) [25].

### Recruitment

Recruitment started in January 2015 and is expected to be completed by July 2016. The target sample size is 110 women. At the point of submission, a total of 50 women were recruited to the trial.

Women will be recruited to the trial in one of three ways:Women attending an antenatal booking clinic in a South East London maternity service who complete the Whooley depression screening questions used routinely in UK maternity services [26] will be approached by a research midwife and asked to take part in a related study on wellbeing in pregnancy, which includes measurement of the prevalence of depression (REC reference: 14/LO/0075). Women who consent to take part in the wellbeing in pregnancy study and who are identified as having depression on the SCID will be asked by a research midwife if they would like to take part in this trial.A woman may be referred to the trial by a midwife in South East London maternity services at a later point in pregnancy (up to 26 weeks gestation) if the midwife suspects that the woman is depressed and may be suitable for the trial. Women can also self-refer (as happens in routine Improving Access to Psychological Therapies (IAPT) care); advertisements about the study will be placed in antenatal clinics, scanning departments and other settings for local pregnant women, e.g. children’s centres. The research midwife will administer the baseline measures to assess eligibility of women for the trial.A woman may self-refer to the trial should she feel she is experiencing symptoms of depression. An advertisement for self-referral to the trial will be positioned in maternity waiting rooms and women’s booking packs, and the research midwife will administer the baseline measures to assess eligibility of women for the trial.

### Assessment of eligibility

The research midwife will outline to women the trial processes and procedures as described in the participant information sheet, and answer any questions that arise. Women will have a minimum of 24 hours to consider if they wish to participate in the trial.

### Randomisation

Women will be randomly assigned to: (1) Guided Self Help (delivered by a Psychological Wellbeing Practitioner) plus usual care or (2) usual care alone (i.e. treatment as usual). Randomisation will be conducted independently of the trial investigators via the UK Clinical Research Collaboration (UKCRC) registered King’s Clinical Trials Unit bespoke web-based central randomisation service. Using a sampling fraction and cut-offs determined from the SCID instrument, collected during a related study on wellbeing in pregnancy (REC reference: 14/LO/0075), we will recruit women in three strata of mild or moderate depression or mixed anxiety depression. To ensure balance, the web-based central randomisation service will allocate women to trial groups (with a 1:1 allocation) using randomly varying blocks, stratified by severity of depression (assessed using scores on the SCID depression scale). The block sizes will not be disclosed, to ensure concealment.

### Allocation to trial groups

Once an eligible woman has given her consent and completed baseline measures, she will be randomised to either Guided Self Help plus usual care, or usual care alone. The research midwife will then communicate information about the allocation group to the participant and, for women allocated to Guided Self Help, will arrange an appointment with the Psychological Wellbeing Practitioner (PWP) to start the intervention.

This trial, being embedded within a related population screening study on wellbeing in pregnancy (REC reference: 14/LO/0075), will allow us to compare the baseline and outcomes of those in the treatment-as-usual group and those receiving treatment as usual though not participating in the trial.

See Additional file 3: Figure S2 for a protocol flow diagram.

## Intervention

### Guided Self Help interventions for depression

Guided Self Help is delivered within the Improving Access to Psychological Therapies (IAPT) programme, which is a large-scale initiative that aims to increase the availability of NICE-recommended psychological treatments for depression and anxiety disorders within NHS-commissioned services in England. It was originally launched in 2008, and key successes in the first three full financial years include more than 1 million people entering treatment, 680,000 people completing treatment and recovery rates in excess of 45 % (with around 65 % showing significant improvement) [24]. IAPT is continuing to expand with plans to be available to at least 15 % of the adult population and to deliver recovery rates of 50 % or more by March 2015 [24].

Two half-time NHS PWPs — Agenda for Change band five, with a post-graduate diploma in low intensity interventions — will be seconded from the IAPT programme and will deliver the trial intervention of Guided Self Help modified for pregnancy. PWPs are UK NHS health service employees who deliver evidence-based low intensity cognitive behavioural therapy (CBT) interventions within the IAPT programme. They have experience in delivering treatment based on Guided Self Help manuals, and in supporting patients’ use of Guided Self Help manuals and relevant freely available resources through regular contact. PWPs are used to carrying a high volume caseload of patients requiring low intensity interventions, and they are experienced in monitoring progress and assessing changes in symptoms; they may signpost to other services if necessary. As part of their role within the IAPT programme, PWPs are required to collect a number of standardised measures including the Patient Health Questionnaire (PHQ-9), Generalised Anxiety Disorder (GAD-7), the Work and Social Adjustment Scale and Phobia Scales. The PWPs are required to possess a range of perinatal competencies in order to successfully deliver the Guided Self Help components of the trial (see the list of competencies in the Appendix).

### Modified Guided Self Help (with usual care) for antenatal depression

A workbook appropriate for pregnancy (available from the corresponding author on request) was developed. In order to establish the components of the intervention, a literature search was carried out to identify studies on risk factors for antenatal depression, moderating factors for poor child outcomes and qualitative studies on women’s experience of antenatal depression. Following this process, key components identified included:Psycho-education about the symptoms and causes of depression with a focus on factors related to pregnancyAn introduction to the cognitive behavioural model and the links between thoughts, feelings and behaviours, and cognitive-behavioural strategies for managing mood, including activity planning, problem solving and thought challengingManaging relationships in the perinatal period, including increasing social support,the development of maternal-fetal attachment and reflecting on how we learn to be parentsHealth and lifestyle factors, including issues involving smoking and nutritionPreparing for parenthood.

The workbook was divided into six chapters, each including a mixture of educational material, testimonials from pregnant women and exercises to be completed by participants. Exercises were based on cognitive behavioural skills, starting with more behavioural interventions such as activity planning and problem solving, and moving on to more cognitive skills such as thought challenging and identifying underlying rules for living. At the end of each chapter a list of homework tasks were suggested, and throughout the workbook there were links to other sources of support, e.g. websites, organisations which provide support or advice to pregnant women, children’s centres and antenatal classes.

Recent evidence suggests that a minimum of four sessions is necessary to achieve good rates of change for low intensity interventions and that dose-response reduces after six sessions [27]. The workbook was therefore designed to be delivered across six sessions; adding an introductory session and a final maintenance session led to an eight-session intervention. Current IAPT practice is to offer sessions lasting between 30–45 minutes, either on the telephone or face to face.

During development, drafts of the workbook were sent to an advisory panel of perinatal experts (psychologists, psychiatrists and midwives) for comments and feedback. A draft was also sent to a panel of service users who were part of an advisory group to a larger perinatal study. These women provided feedback on wording, relevance and use of examples and layout, and the workbook was modified accordingly. The workbook was piloted by one of the authors (JD) in routine IAPT care; ten women took part in the pilot to assess the feasibility of delivering the intervention during pregnancy, the acceptability of the content to pregnant women and preliminary outcomes. Based on women’s feedback, a number of amendments were made: the text was edited to reduce the number of words; the title was changed to ‘Wellbeing in Pregnancy’ (several women commented on the original title of the workbook, ‘Antenatal Depression’, which they felt was unhelpful due to possible stigma and their associations with more severe forms of perinatal disorders); specific references were made to how different sections were relevant to women who already have children; and the health chapter was adapted to be more focussed on overcoming barriers to good health behaviours (several women felt the chapter on health repeated messages they had from midwives and had less of a warm tone than other chapters). Women reported needing the sessions to motivate them and engage with the material; i.e. they indicated that they may not have completed the workbook on their own. The routinely collected scores on measures of anxiety (GAD-7) and depression (PHQ-9 and EPDS) reduced following the intervention.

Prior to delivering this Guided Self Help intervention within this pilot RCT, the two PWPs were trained in the modified intervention (and subsequently supervised on a weekly basis) by an experienced perinatal clinical psychologist. They were also trained in associated areas relevant to perinatal clinical work including safeguarding, violence and abuse, smoking cessation and the mother-child relationship [21]. The two PWPs will collect the same standardised measures as they would within an IAPT setting — Patient Health Questionnaire (PHQ-9), the Generalised Anxiety Disorder scale (GAD-7), the Work and Social Adjustment Scale and Phobia Scales — at every Guided Self Help session they have with trial participants.

The Guided Self Help (with usual care) intervention for antenatal depression comprises an initial session at the beginning of therapy followed by up to eight 30-minute sessions, delivered weekly where possible. The PWPs will also conduct an additional session, at six to eight weeks post-delivery (i.e. before the post-delivery research outcomes are collected). The first Guided Self Help session will be delivered face to face, and the subsequent sessions will either be delivered face to face or over the telephone, based on the participants’ preferences.

Based on existing evidence from trials of Guided Self Help [27], a minimum number of four sessions is required to determine reliable and clinically significant improvements. Women who show no improvement in symptoms at the end of the Guided Self Help sessions and who want further support will be referred by the PWP either for high intensity interventions or to their general practitioner (GP), as is the usual clinical practice. Women who show significant deterioration in symptoms on the routinely collected measures — at any point during or at the end of the Guided Self Help sessions — will be discussed in the PWPs’ clinical supervision (or in more urgent situations, the nominated senior psychologist available for emergencies) and referred as appropriate to GPs, high intensity psychologists or secondary care.

### Treatment as usual

The findings of local audits and a recent study [18] indicate that very few pregnant women are referred for psychological therapy in routine practice. We will record any referrals that occur, treatment received and other interventions accessed (e.g. third sector support, antidepressants) for women in both groups of the trial (at the two follow-up points).

## Outcomes

### Primary outcome

The primary outcome is the score for Edinburgh Postnatal Depression Scale (EPDS) depressive symptoms at 14 weeks post-randomisation.

### Key secondary outcomes

#### At 14 weeks post-randomisation

At 14 weeks post-randomisation, the secondary outcomes are:Proportion of participants meeting PHQ-9 criteria for depression (i.e. score of ≥10)Proportion of participants meeting GAD-7 criteria for anxiety (i.e. score of ≥8).

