## Sample size

This is primarily a feasibility trial, but we also carried out a sample size calculation to allow us to calculate what preliminary evidence we could generate on efficacy. Assuming a correlation of 0.4 between baseline and outcome EPDS symptom score, a two-arm parallel-group design with 52 women in each arm, the Stata procedure *sampsi* gives 79 % power to detect a difference of 0.5 SD using ANCOVA and a two-tailed test using a 95 % significance level (based on an effect size of 0.31, as this was found in a systematic review of Guided Self Help in non-maternity settings [22]). We aim to recruit 110 women. The study would have 66 % power to detect a difference in the caseness rate of recovery of 35 % in controls versus 60 % in the Guided Self Help arm.

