An odds ratio and 95 % CI for recovery, defined within IAPT as a PHQ-9 score of ≥10 at 14 weeks post-randomisation, will be estimated. We will compare groups for continuous scores on the EPDS at 14 weeks post-randomisation and 3 months post-delivery. The variance estimates will assist in power calculations for a definitive trial. Supplementary analyses will estimate complier average causal effects for a binary measure of compliance to treatment using the instrumental variable method. Therapist effects will be evaluated. Infant growth will be explored using random effects growth curve models (*xtmixed* in Stata) to compare birth and growth velocities of the groups.

Qualitative data will be coded in NVivo8 [37] following the principles of framework analysis [38], which includes the identification of a thematic framework, the abstraction and synthesis of key themes and the mapping and interpretation of the dataset as a whole. Qualitative results will be discussed within the context of quantitative data interpretation.

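### The 14-week PHQ-9 and GAD-7 outcomes are defined as cut-off proportions with no score analysis stated, which costs precision, chiefly for anxiety

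*Protocol article*

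**What the plan says.** Under Key secondary outcomes, the article gives two outcomes at 14 weeks post-randomisation, and both are binary: "Proportion of participants meeting PHQ-9 criteria for depression (i.e. score of ≥10" and "Proportion of participants meeting GAD-7 criteria for anxiety", the latter at a score of 8 or more.

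The Statistical analysis section plans an odds ratio with a 95% confidence interval for recovery, "defined within IAPT as a PHQ-9 score of ≥10 at 14 weeks post-randomisation, will be estimated". Its next sentence is "We will compare groups for continuous scores on the EPDS at 14 weeks post-randomisation and 3 months post-delivery". It mentions no comparison of PHQ-9 or GAD-7 scores, and it describes no analysis for GAD-7 in particular. The primary EPDS score is analysed by ANCOVA with its baseline value.

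The Sample size section gives 79% power for 0.5 SD on the EPDS (52 per arm, baseline correlation 0.4). For the binary outcome it gives 66% "power to detect a difference in the caseness rate of recovery of 35" per cent in controls against 60% with Guided Self Help.

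The Background section names estimation of treatment effect sizes as an objective. Its third aim covers other outcomes, including psychological symptoms after treatment and after delivery, and it says effect sizes will be estimated for that aim too.

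**The concern.** A proportion above a cut-off yields neither a mean difference nor a standard deviation, and these are what a Phase III calculation on a symptom score needs. For depression the loss is limited, because the EPDS score is the primary outcome and is analysed efficiently. For anxiety, GAD-7 caseness is the only outcome in the article's listed primary and key secondary outcomes. Yet mixed anxiety and depression is one of the recruited strata.

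The entry criteria add to this. Women are enrolled on a SCID diagnosis, not on a GAD-7 score, so some may start below 8. Such a woman can move to the case side by worsening, but no improvement in her anxiety can show on this outcome. The article does not say how many such women to expect.

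**Working it through.** **Inputs.** From Sample size: 52 per arm, two-sided 5% level, baseline correlation r = 0.4 (stated for the EPDS), target effect 0.5 SD, rates 35% and 60%. Assumptions not in the documents: a normal underlying score, and a control rate of 35% on the non-case side of the cut-off. I read 35% and 60% as proportions recovered. Power is the same if they are read as their complements.

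**Step 1: reproduce the stated powers.**

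- EPDS by ANCOVA: SE = √(2/52 × (1 − 0.4²)) = 0.180 SD. Power = Φ(0.5/0.180 − 1.96) = 79.4%. Stated: 79%.
- 35% v 60%, uncorrected: (0.25 × √52 − 1.96 × √(2 × 0.475 × 0.525)) / √(0.35 × 0.65 + 0.60 × 0.40) = 0.612, so power is 73.0%.
- With continuity correction: effective n = 52 × (1 − 1/(52 × 0.25))² = 44.3 per arm, which gives 65.9%. Stated: 66%.

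Both figures reproduce, the second as a continuity-corrected one.

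**Step 2: information kept by a cut-off.** Relative to a comparison of the normal score, a cut-off with a proportion p on one side keeps φ(z_p)² / (p(1 − p)). To compare with ANCOVA, multiply by 1 − 0.4² = 0.84.

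| Case proportion | Kept v unadjusted score | Kept v ANCOVA, r = 0.4 |
|---|---|---|
| 50% | 0.637 | 0.535 |
| 40% or 60% | 0.622 | 0.522 |
| 35% or 65% | 0.603 | 0.507 |
| 30% or 70% | 0.576 | 0.484 |

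The cut-off alone therefore loses 36 to 42%. Against a baseline-adjusted score analysis the loss is 46.5 to 51.6%. The second range contains the first, so the two must not be added.

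**Step 3: power on the same women, 52 per arm.** The pair 35% v 60% corresponds to z(0.60) − z(0.35) = 0.64 SD. A 0.5 SD shift moves 35% to Φ(z(0.35) + 0.5) = 54.6%.

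| Effect | Cut-off (continuity-corrected) | Score, unadjusted | Score, ANCOVA r = 0.4 |
|---|---|---|---|
| 0.64 SD | 73% (66%) | 90% | 94% |
| 0.5 SD | 52% (44%) | 72% | 79% |
| n per arm for 80% power at 0.5 SD | 101 (111) | 63 | 53 |

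The like-for-like comparison uses the uncorrected cut-off figures. At 0.5 SD, using the score gains 20 points (52% to 72%), and baseline adjustment adds 7 (72% to 79%). Most of the gain therefore does not depend on borrowing r = 0.4 from the EPDS.

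**The case against.** **The article is condensed, and its analysis plan is not shown.** A reader might infer that PHQ-9 and GAD-7 will never be analysed as scores and that baseline values will be ignored. The article says neither. It does not call the odds ratio unadjusted, a logistic model can carry a baseline covariate, and such covariates are commonly left to the analysis plan. The full list of measures is in a supplementary table that is not shown, and the third aim speaks of effect sizes for symptoms. All of this stands. What remains is that the article itself fixes the form of the two key outcomes as proportions and names the EPDS alone for continuous comparison.

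**The cut-offs are meaningful.** They describe caseness, the article ties the PHQ-9 one to IAPT practice, and IAPT results are reported as recovery rates. This stands, and it is a reason to keep the proportions. A PHQ-9 score would also be a second continuous depression measure beside the EPDS, so the case for it is weaker than for GAD-7.

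**Two stronger readings fail.** One is that half the information is lost and baseline adjustment is lost on top. The figure of about half already includes the baseline adjustment. The other is that a woman who starts below a cut-off counts as a non-case whatever happens. The outcome is status at 14 weeks, so she becomes a case if she worsens past the cut-off. What she cannot do is show improvement.

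**The inputs are borrowed.** No baseline correlation is given for PHQ-9 or GAD-7, and the 35% and 60% rates concern recovery, which the article links to PHQ-9. Applying them to GAD-7 is an extrapolation. The table in step 2 shows that the loss varies little across case proportions of 30 to 70%.

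**Conclusion.** The point holds as a cheap improvement of modest weight. The stated outcomes are a less efficient use of scores that must be obtained anyway to compute the proportions, and they do not deliver the effect sizes on symptom scores that the trial wants for planning. With a normal underlying score, the cut-off alone loses about 36 to 42% of the information at case proportions of 30 to 70%. At 0.5 SD and 52 per arm, power is 52% (44% corrected) against 72% for the score. The 79% for ANCOVA, and the 46.5 to 51.6% loss relative to it, hold only if r = 0.4 applies to these scales.

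The point matters most for GAD-7. For PHQ-9 it is minor, because the primary EPDS analysis already treats depression severity as a continuous score. It does not affect the primary analysis or the validity of the proportions.

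**What to change.** Keep the PHQ-9 and GAD-7 proportions as the listed key secondary outcomes. Add to the analysis plan, as pre-specified secondary estimates, the between-group differences in mean 14-week GAD-7 and PHQ-9 scores with confidence intervals, using the same baseline-adjusted ANCOVA as for the EPDS. Report the score SDs and baseline correlations with them, for use in Phase III planning. If only one is added, it should be GAD-7.

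The cost is a sentence or two and two regressions. The downside is two more secondary estimates to report. The abstract says that depression and anxiety measures other than the EPDS are collected before allocation but does not name them, so the sponsor should confirm that both scales are among them. The sessional scores taken by the practitioners cannot serve, because they exist in one arm only. If a baseline score is missing by design, the unadjusted score comparison still keeps most of the gain. With 50 of 110 women recruited at submission and no interim analysis planned, there is still time to pre-specify this.
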